### Outcomes

#### Primary outcome

Participants’ overall symptomatology will be evaluated with the Rivermead Post-Concussion Symptoms Questionnaire (RPQ). RPQ is a simple questionnaire composed of 16 concussion symptoms rated by patients which evaluates cognitive, physical and emotional symptoms according to their severity. It has been demonstrated that when the entire 16-item questionnaire is summated together there is a poor overall fit to the Rasch model, suggesting all 16 items do not tap into the same underlying construct [30]. However, when split into two separate scales, the RPQ-3 has shown moderate test-retest reliability and RPQ-13 has shown good test-retest reliability and each set of items forms a unidimensional construct for people with head injury at three months post-injury [30, 31]. The RPQ-3 is associated with early symptom clusters of post-concussive symptoms (scored 0–12), and the RPQ-13 is associated with having a greater impact on participation, psychosocial functioning, and lifestyle (scored 0–52), with a higher score representing a greater impact [31].

#### Secondary outcomes

The secondary outcome measures include a quantitative EEG measuring three ERPs (brain vital sign framework), the Neck Disability Index (NDI), and the Patient Health Questionnaire-9 (PHQ-9).

### Brain vital sign

Brain vital sign will be measured by rapid advanced electroencephalography (EEG) via NeuroCatch™. Specifically, the three ERPs, auditory N100 (auditory sensation); auditory oddball P300 (basic attention); and auditory speech processing N400 (cognitive processing) will be evaluated. Standardized normative data exists for all three ERP responses [32–34].

### Neck Disability Index (NDI)

Neck-related disability will be measured via the NDI. The NDI is a 10-item questionnaire, which examines the impact of self-reported neck pain on various activities of daily living. The responses are summed for a total ranging from 0 to 50 with a higher score representing a more severe perceived disability. The questionnaire has demonstrated reliability, construct validity and responsiveness to change in various populations [35].

### Patient Health Questionnaire-9 (PHQ-9)

A screening form for depression and anxiety via the PHQ-9 will be administered. The PHQ-9 has been shown to have adequate reliability and good validity for the concussion population as well as the spinal pain population [36–39].

All outcome measures will be compared to participants’ values at baseline, 6-week re-assessment and trial end-point assessment.

### Statistical analysis

The primary outcome is a change in symptoms following rehabilitative interventions using the RPQ. Previous research examining the internal construct validity of the Rivermead Post-Concussion Symptom Questionnaire suggested that a score of 2 or more on at least 3 of the 16 symptoms represents an unfavourable outcome [40]. We chose to calculate the study sample size by assuming an effect size. Unfortunately, to date, no validated change scores exist, thus we prescribed a cut-off of 15% improvement as minimal clinically importance difference (MCID). This translates into a change of 2 points on the RPQ-3 and a change of 8 points on the RPQ-13. This agrees with prior clinical literature examining changes post-intervention on concussion symptoms [41]. Based on this effect size, a power of 80%, a significance level at *p* < 0.05 and a two-sided t-test, we calculated that a sample size of 50 participants was necessary [42].

Descriptive statistics will be applied to all outcome measures to assist in summarizing the results. Participant demographic data will be compared to assess compatibility between groups, specifically before the crossover point.

The statistical analysis conducted in this research is composed of an adjusted model using an analysis of variance to test for associations between variables and outcomes (two groups [personalized care or usual care] x 3 times [baseline, week 6 and 12]) [42]. The statistical analysis conducted in this study will be made using SAS OnDemand for Academics 2021. The data set is composed of six variables, two independent variables –personalized care group or usual care group – and four dependent variables – age, sex, and result of treatment on the RPQ graded as total score and sub-classification (RPQ-3 and RPQ-13). A 2-way analysis of covariance (ANCOVA) (two groups [personalized care or usual care] x 3 times [baseline, week 6 and 12] x baseline secondary outcomes [ERPs, NDI and PHQ-9] will be used to examine the effects of the rehabilitation programs while controlling for these covariates. Lastly, an unpaired t-test will be used to assess the effects of the rehabilitation programs on the secondary outcomes. In addition to the per-protocol analysis, an intention-to-treat analysis will be conducted.

All unintended effects, harms and/or dropouts during the program will be recorded.

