**Methods:**

We will conduct a multi-center 12-week case-crossover randomized controlled trial. 50 participants will be recruited from out-patient University Health Network clinics and community-based clinical practices around the greater Toronto area. Participants will be randomized at baseline to Group A: a personalized care program followed by an active control or Group B: an active control followed by a personalized care program. Participants will be included should they be 21 years of age and older and have symptoms that have persisted beyond 4 weeks but less than 1 year. Participants will undergo 6-weeks of care in their respective streams. After 6-weeks, participants will undergo a re-examination. They will then crossover and undertake the alternative treatment for 6 weeks. At the end of 12 weeks, participants will undertake the endpoint examinations. The primary outcome will be the Rivermead Postconcussion Questionnaire (RPQ). The secondary outcomes will be changes in standardized clinical examination, Neck Disability Index (NDI), Patient Health Questionnaire (PHQ-9) and an electroencephalography (EEG) via NeuroCatch^™^. The statistical analysis to be performed is composed of an adjusted model using an analysis of variance, specifically using an unpaired t-test to test for associations between variables and outcomes.

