### Study design

We will be conducting a 12-week case-crossover randomized controlled trial (see Table 1). At baseline, following the standardized examination, completion of the primary outcome measure (RPQ), baseline quantitative EEG and secondary outcome measures (NDI and PHQ-9), participants will be randomized to either Group A: a personalized care program followed by an active control or Group B: an active control followed by a personalized care program. No washout period will be used between interventions. It was assumed that given both interventional groups have a focus on rehabilitative therapy that no wash-out period was needed. Participants will undergo 6 weeks of care in their respective streams. After 6 weeks, participants will undergo a re-examination. They will then crossover and undertake the alternative treatment for 6 weeks. At the end of 12 weeks, participants will undertake the endpoint examinations.

**Table 1 Tab1:** Enrolment schedule, interventions and assessments

	Study Period						
	Enrolment/Baseline assessment	Allocation	T1	Mid-point assessment (6 weeks)	Cross-over	T2	End-point assessment (12 weeks)

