### Randomization and masking

We will use simple randomization to allocate participants to one of two sequences of interventions: Group A: personalized care program followed by active control; or Group B: active control followed by personalized care program. The study coordinator (NM) conducted the randomization using a randomized table generator (GraphPad Software Inc, La Jolla, CA). Randomization will be concealed; no other study personnel will be aware of the intervention assignments. However, it was not possible to blind the study coordinator (NM) as they are one of the main treating clinicians. Additionally, it was not possible to ensure adequate blinding of the participants, given the necessary thorough description of the treatment procedures that occurred during the informed consent process.

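### The RPQ is analysed with a parallel-group group-by-time layout in a two-sequence crossover; 'group' is undefined and no contrast is named that estimates personalised minus usual care

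*Protocol article*

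**What the plan says.** The design is a two-sequence, two-period crossover. Under Randomization and masking: "We will use simple randomization to allocate participants to one of two sequences of interventions". Group A receives personalised care and then the active control; Group B receives them in reverse order. Under Study design, after the week-6 re-examination: "They will then crossover and undertake the alternative treatment for 6 weeks". The same section adds: "No washout period will be used between interventions".

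The Statistical analysis section describes an "adjusted model using an analysis of variance to test for associations between variables and outcomes" with the factors "two groups [personalized care or usual care] x 3 times [baseline, week 6 and 12". The independent variables are listed as "personalized care group or usual care group". An ANCOVA with the same group and time factors, plus baseline ERPs, NDI and PHQ-9, "will be used to examine the effects of the rehabilitation programs while controlling for these covariates". Secondary outcomes are compared by unpaired t-test. The Methods part of the abstract describes the analysis of variance as "specifically using an unpaired t-test to test for associations between variables and outcomes".

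The article does not label the ANOVA as primary. That is inferred, because the RPQ is the primary outcome and this is the first model given for it.

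**The concern.** A table of two groups by three times suits a trial in which each participant keeps one treatment throughout. Here nobody does, and neither meaning of group fits:

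- **Randomised arm.** From week 6 to week 12 the participants labelled personalised care are on usual care, and the reverse.
- **Treatment being received.** There is no treatment at baseline, so the first column of the layout cannot be filled. Each participant also appears under both labels, so an unpaired comparison does not apply.

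The text does not say whether the group effect, the interaction or a single-time contrast answers the primary question. These answer different questions, and one of them can be close to zero when the programme works. Without a named contrast, the deciding term could be chosen after the data are seen.

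**Working it through.** **Inputs from the article.** Total N = 50; 80% power; two-sided 0.05; t-test; target difference 8 points on RPQ-13 (2 on RPQ-3); assessments at baseline, week 6 and week 12.

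**Assumptions.** 25 per sequence (simple randomisation does not guarantee this). Equal SD and equal within-person correlation ρ at all three times, with ρ = 0.3, 0.5, 0.7. The article gives no SD and no correlation.

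**Step 1: the plan's own figure.** N = 50 cannot be reproduced without an SD, so the SD is back-solved. With 25 per group, an unpaired t-test has 80% power at a standardised difference of 0.809. That gives SD = 8/0.809 = 9.9 on RPQ-13 and 2/0.809 = 2.5 on RPQ-3. Forward check by the normal formula with SD 10: n per group = 2 × (1.960 + 0.842)² × (10/8)² = 24.5, rounded up to 25, total 50. The total is sensitive to the SD: 8 gives 32 and 12 gives 72. A paired test at d = 0.4 also needs about 50 (49.06 before rounding up), so N = 50 does not show which design was assumed.

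**Step 2: expected differences.** Let δ be the Group A minus Group B difference at week 6, with benefit counted as positive, and D12 the same difference at week 12. At baseline the expected difference is 0 by randomisation. D12 depends on carryover: 0 if first-period gains persist fully and the sequences end level, −δ if there is no carryover, −δ/2 midway.

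**Step 3: group main effect, with group as the arm.** Effect = (0 + δ + D12)/3. For δ = 8:

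- full persistence: (0 + 8 + 0)/3 = 2.67 points, or δ/3
- midway: (0 + 8 − 4)/3 = 1.33 points, or δ/6
- no carryover: (0 + 8 − 8)/3 = 0

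The participant mean over three times has variance SD² × (1 + 2ρ)/3. At ρ = 0.5 with full persistence, the standardised effect is (0.809/3)/√(2/3) = 0.330 and the noncentrality is 0.330 × √(25/2) = 1.17. On 48 df this gives 20.8% power.

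**Step 4: group-by-time interaction (2 df).** Noncentrality = (25/2) × Σ(difference − mean difference)²/[SD² × (1 − ρ)]. At ρ = 0.5 with full persistence this is 12.5 × 0.809² × (2/3)/0.5 = 10.9, and power is 83.7%. The sum of squares is 42.67 for differences of (0, 8, 0), and also for (0, −8, 0) and (0, 0, 8). The F test therefore cannot tell a benefit at week 6 from a harm of the same size, or from a difference that appears only in the second period.

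**Step 5: week-6 ANCOVA on baseline RPQ.** It targets δ whatever happens after the switch. Standardised effect = 0.809/√(1 − ρ²). At ρ = 0.5 this is 0.934, and power is 89.9%.

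| Power | ρ = 0.3 | ρ = 0.5 | ρ = 0.7 |
|---|---|---|---|
| Group main effect, full persistence | 24.9% | 20.8% | 18.1% |
| Group main effect, midway | 9.8% | 8.8% | 8.2% |
| Group main effect, no carryover | 5% | 5% | 5% |
| Interaction, full persistence | 69.0% | 83.7% | 97.2% |
| Interaction, no carryover | 99.3% | >99% | >99% |
| Week-6 ANCOVA, any carryover | 83.6% | 89.9% | 97.5% |

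**Step 6: what a two-period analysis estimates.** A contrast of end-of-period levels gives (δ − D12)/2: 4 of 8 points with full persistence, 8 with no carryover. A contrast of within-period changes gives (2δ − D12)/2: 8 points with full persistence, 12 with no carryover. Each equals δ only under its own carryover assumption.

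**The case against.** The strongest reply is that the model already contains what is needed. The time factor carries the period effect. If group means the arm, it is the sequence factor, because Groups A and B are sequences. In a two-sequence crossover the treatment effect lies in the sequence-by-period contrasts, so a group-by-time model with its interaction includes it; the week-6-minus-baseline group difference is one linear contrast of that model. This stands. A reader might infer that the model lacks any period or sequence term, and the text does not support that. What is missing is an identifiable current-treatment term and a named contrast.

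Second, the article never says that the group main effect decides anything. A reader might infer that the trial has about 20% power where 80% was planned. That does not follow: the 80% is stated for a t-test, and the interaction, the natural test of differential change, keeps most or all of the power. It is also a valid test of no difference of any kind, since equivalent programmes would leave the sequences exchangeable at all three times. This stands too, but a 2-df test gives neither direction nor size, and the stated objective is whether personalised care does better.

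Third, a reader might take the zero difference at week 12 as a property of the design. It holds only if first-period gains persist fully, which the article does not state; with less carryover the main effect is diluted further.

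Fourth, the variable list is weak evidence. It also omits time, ERPs, NDI and PHQ-9, which the models use, so the absence of a sequence variable from it proves little.

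Finally, exact model terms are often left to an analysis plan that is not shown. That would cover silence. Here the article states the factors and their levels, and they do not match its own design.

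**Conclusion.** The point holds as a mismatch between the stated model and the design. Group has no meaning that fits all three times, and no contrast is named that estimates personalised minus usual care. Read as the treatment effect, the group main effect would be δ/3 with full persistence (power about 18-25%) and zero with no carryover (5%). The interaction keeps about 69-97% power or more but does not estimate the effect.

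The multiples of δ follow from the layout and the carryover assumption alone. The power figures also rest on the back-solved SD (about 10 on RPQ-13, 2.5 on RPQ-3), ρ between 0.3 and 0.7, and 25 per sequence. The documents do not show that the main effect will be used, so the low power is the consequence of one permitted reading and not a finding about the trial's power.

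**What to change.** 1. Define group as the randomised sequence (A or B) wherever it appears, including the ANCOVA with baseline ERPs, NDI and PHQ-9 and the unpaired t-tests, and bring the abstract into line.
2. Make the primary analysis an ANCOVA of week-6 RPQ on sequence, adjusted for baseline RPQ. Baseline then enters as a covariate and not as an outcome level. Under the assumptions above, power is about 84-97%, and the switch cannot contaminate the estimate.
3. Report any two-period mixed model (treatment, period, sequence, random participant) only as secondary or sensitivity. State that a contrast of end-of-period levels gives about half the effect if first-period gains persist, or use within-period changes with the carryover assumption written down.
4. Record sequence and period as variables in the data set.

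The cost is wording and a few lines of code; the assessments are already scheduled. The downside is that second-period data do not enter the primary test.

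### The RPQ is analysed as three scores under a single 0.05 level, with no primary score or success rule named, and the total conflicts with the protocol's own case against summing the items

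*Protocol article*

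**What the plan says.** The Statistical analysis section opens with "The primary outcome is a change in symptoms following rehabilitative interventions using the RPQ" and names no particular score. Its list of variables then gives "result of treatment on the RPQ graded as total score and sub-classification (RPQ-3 and RPQ-13", that is, three results. The hypothesis under Objectives speaks of improved RPQ scores in the plural and sets no rule for which of them must improve.

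The Primary outcome section argues against the summed score: "when the entire 16-item questionnaire is summated together there is a poor overall fit to the Rasch model". For RPQ-3 and RPQ-13 it says that "each set of items forms a unidimensional construct for people with head injury at three months post-injury". It reports good test-retest reliability for RPQ-13 and moderate for RPQ-3.

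Table 1 has rows for RPQ-3 and RPQ-13 and none for the total. The minimal important difference is likewise given for the two sub-scales only: "This translates into a change of 2 points on the RPQ-3 and a change of 8 points on the RPQ-13".

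The only significance level is in the sample-size sentence: "a power of 80%, a significance level at *p* < 0.05 and a two-sided t-test, we calculated that a sample size of 50 participants was". Nothing splits that level across scores or orders the tests.

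**The concern.** A primary outcome has to identify the one result, or the stated combination of results, on which the trial is judged. Here three candidates share one alpha, one power and one sample size. After the data are in, a significant difference on any of them could be presented as the primary finding, and the text would not rule it out.

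The total raises a second problem. The protocol gives a measurement reason not to sum the 16 items and then analyses the sum. A result on the total would have no stated threshold for clinical importance and, by the protocol's own account, no single construct behind it.

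At stake is whether the stated 5% error and 80% power describe the primary outcome as written.

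**Working it through.** **1. What each part of the protocol supports**

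| Place | Total | RPQ-3 | RPQ-13 |
|---|---|---|---|
| Primary outcome section | poor Rasch fit | one construct, moderate reliability | one construct, good reliability |
| Table 1 | no row | row | row |
| MCID | none | 2 points | 8 points |
| Variables analysed | listed | listed | listed |

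The total appears only in the last row.

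**2. The MCIDs.** The stated rule is "we prescribed a cut-off of 15% improvement as minimal clinically importance difference (MCID". 15% of 12 is 1.8, rounded to 2; 15% of 52 is 7.8, rounded to 8. So the effect size was set on the two sub-scales.

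**3. The sample size of 50.** No SD is given, so the figure cannot be reproduced directly and the effect is back-solved.
- Normal approximation, total N = 4(z₀.₉₇₅ + z₀.₈₀)²/d². With N = 50, d = 2 × (1.960 + 0.842)/√50 = 0.79. The noncentral t with 25 per group gives d = 0.81.
- Implied SDs: 2/0.81 ≈ 2.5 for RPQ-3 and 8/0.81 ≈ 9.9 for RPQ-13.
- With SDs of 2.5 and 10, d = 2/2.5 = 8/10 = 0.8, and 4 × 7.85/0.64 = 49.1, or 50 after rounding each group up to 25.

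Thus 50 fits one test at two-sided 0.05 on either sub-scale, with no allowance for a second or third.

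**4. Error rate if any score counts.** Assumptions, none of them in the documents: SDs of 2.5 and 10; correlation r between the RPQ-3 and RPQ-13 test statistics; each score tested at two-sided 0.05; success if at least one is significant. Simple two-group z-tests were simulated under no effect, with 2,000,000 draws per setting.

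| r | RPQ-3 or RPQ-13 | RPQ-3, RPQ-13 or total |
|---|---|---|
| 0 | 9.8% | 10.7% |
| 0.3 | 9.5% | 10.1% |
| 0.5 | 9.1% | 9.4% |
| 0.6 | 8.8% | 9.0% |
| 0.7 | 8.4% | 8.5% |
| 0.8 | 7.8% | 7.9% |
| 0.9 | 7.1% | 7.1% |

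Check at r = 0 for two scores: 1 − 0.95² = 9.75%. The other SD pairs tried (3 and 10, 3 and 12, 2.5 and 13, 4 and 10) give at most 11.0%. Three independent tests would give 1 − 0.95³ = 14.3%, which does not apply because the total is the sum of the other two.

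**5. What the total adds.** At r = 0 its correlation with RPQ-13 is 10/√(2.5² + 10²) = 0.97, and it is higher for larger r. It therefore adds 10.7 − 9.8 ≈ 0.9 points at most with these SDs, and almost nothing at r = 0.9.

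**6. Power under other rules.** Suppose each sub-scale has 80% power at 0.05.
- Both required: the error does not exceed 5%. Joint power lies between 0.8 × 0.8 = 64% (independent) and 80% (perfectly correlated).
- Equal alpha split, d = 0.81, 25 per group: power per score is 71% at 0.025 and 65% at 0.0167. Restoring 80% would take 62 and 68 participants.

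**The case against.** The strongest reply is that the protocol never says each score is tested at 0.05, nor that success on any one is enough. Its single alpha belongs to the sample-size calculation. If all scores had to be significant, the error would stay at or below 5%. A multiplicity rule may sit in an analysis plan that is not shown. All of this stands, and it limits what can be said about the error rate.

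The list naming the three results is also loosely worded: it calls age and sex dependent variables. Table 1 and the MCIDs suggest that two scores were really intended. That is a fair reading, but it does not help the text as it stands, since the same section still lists the total as a result of treatment.

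The planned RPQ analyses are a group-by-time analysis of variance and an analysis of covariance. The Statistical analysis section assigns the unpaired t-test to the secondary outcomes, although the abstract is looser. The simulation therefore illustrates the multiplicity and does not model the planned analysis.

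Two stronger readings are tempting. A reader might infer that the trial's false-positive rate is 9% to 11%. The documents do not support that: no decision rule is stated, no correlation is given, and the figure drops below 9% once the correlation passes about 0.6. A reader might also infer that the total is the main source of inflation. It is not; nearly all of it comes from having two sub-scales.

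What survives is that the primary score is not identified. That cannot be left to an analysis plan, because the sample size in this document depends on it.

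**Conclusion.** The point holds as a defect in the definition of the primary outcome. Three RPQ results are carried under one two-sided 0.05 level with no primary score and no success rule. One of them, the total, contradicts the protocol's own account of the scale and lacks both an MCID and a row in Table 1. This rests on the text alone.

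The size is conditional. If a win on any score counted, the error would be about 7% to 11% in place of 5%, over the whole assumed correlation range, and about 7% to 10% without the total. Dropping the total would therefore cure the internal conflict but leave most of the multiplicity. If both sub-scales were required, the error would hold and the 80% power would generally not.

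**What to change.** State in the protocol which RPQ score decides the trial, by one of these routes:

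- **Hierarchical.** Name one primary score, for example RPQ-13, for which the protocol reports the better test-retest reliability. Test RPQ-3 at two-sided 0.05 only if RPQ-13 is significant. The familywise error for the two stays at 5%, and RPQ-13 keeps the full alpha assumed in the sample-size sentence.
- **Co-primary.** Keep RPQ-3 and RPQ-13 together with a written rule: both required, or Holm.

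In either case report the 16-item total descriptively, without a confirmatory test.

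Costs: under the hierarchical route a result on RPQ-3 alone can no longer be claimed as confirmatory. Requiring both sub-scales lowers power to between 64% and 80% at the implied effect. Holm leaves the power for a given score between 71% and 80%, since its first step uses 0.025 and its second 0.05. Either co-primary route needs the sample size restated.

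The choice should be fixed before outcome data are examined. The time point of the primary comparison in this crossover is a separate question, and this change does not settle it.

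### The RPQ analysis is named as a group-by-time ANOVA/ANCOVA, called an unpaired t-test in the abstract, with no within-participant structure; fitted as named, its tests have the wrong error rate

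*Protocol article*

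**What the plan says.** Under Study design in the protocol article, participants are randomized to one of two sequences, change programme at week 6 and finish at week 12. Table 1 schedules the RPQ-3 and RPQ-13 at baseline, week 6 and week 12. The Outcomes section confirms the repeated scoring: "All outcome measures will be compared to participants’ values at baseline, 6-week re-assessment and trial end-point assessment".

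The Statistical analysis section names the RPQ model twice. First it is "an adjusted model using an analysis of variance to test for associations between variables and outcomes (two groups [personalized care or usual care] x 3", where the three are the assessment visits. Then it is "A 2-way analysis of covariance (ANCOVA) (two groups [personalized care or usual care] x 3 times [baseline, week 6 and 12", with baseline ERPs, NDI and PHQ-9 as covariates. That section gives the unpaired t-test to the secondary outcomes. The abstract instead attaches it to the main model: "an adjusted model using an analysis of variance, specifically using an unpaired t-test to test for associations between variables and outcomes".

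None of these descriptions uses the terms repeated-measures, mixed or within-participant, or names a participant effect or covariance. None names sequence or period.

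**The concern.** The participant is the unit of randomization, and each gives three correlated RPQ scores. A model with only group, time and their interaction pools all the variation around the cell means into one residual. That residual mixes stable differences between people with visit-to-visit variation within people, and it is the right yardstick for neither test. A comparison of sequence averages needs the between-person variation. A comparison of change, or of the two treatments within a person, needs the within-person variation.

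At stake are the p-values and confidence intervals of the primary outcome. They would be wrong in a direction that depends on which term is reported.

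**Working it through.** **Inputs from the protocol article (Statistical analysis).** Two-sided test, "a significance level at *p* < 0.05"; power: "Based on this effect size, a power of 80"%; total size: "and a two-sided t-test, we calculated that a sample size of 50 participants was necessary"; target difference: "This translates into a change of 2 points on the RPQ-3 and a change of 8 points on the RPQ-13". Three scores per person (Table 1).

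**Assumptions.** 25 per group; complete data; equal correlation ρ between any two visits, taken as 0.3, 0.5 and 0.7 because the article gives none; no covariates. The article also gives no SD, so its figure of 50 cannot be reproduced from stated inputs alone. It does follow for the RPQ-13 with an SD of about 9.9: 8/9.9 = 0.81, and a t-test of 25 against 25 then has 80% power. That SD is used for the power step only.

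**Degrees of freedom.** Fitted without a participant term: 50 × 3 = 150 rows less 6 cell means = 144 for every test. With participant as the unit: 50 − 2 = 48 for group, and 2 × 48 = 96 for group-by-time.

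**1. Group (sequence) main effect under the null.** The variance of a person's three-visit mean is (1 + 2ρ) times what independence would give. The actual rejection rate is about P(|Z| > 1.96/√(1 + 2ρ)).
- ρ = 0.3: 1.96/√1.6 = 1.55, giving 12.1%
- ρ = 0.5: 1.96/√2.0 = 1.39, giving 16.6%
- ρ = 0.7: 1.96/√2.4 = 1.27, giving 20.6%

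Two simulations of 20,000 trials per setting gave 12.3%, 16.7%, 20.4% and 11.9%, 16.8%, 20.9%. With the between-person error term the rate was about 5%.

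**2. Group-by-time under the null.** The interaction statistic is shrunk by (1 − ρ). With 2 df the rejection rate is about exp(−5.991/[2(1 − ρ)]).
- ρ = 0.3: 1.4%
- ρ = 0.5: 0.25%
- ρ = 0.7: below 0.01%

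The simulations gave 1.6%, 0.3%, 0.0% and 1.4%, 0.3%, 0.0%. With the within-person error term the rate was about 5%.

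**3. If group means treatment received (weeks 6 and 12).** The treatment contrast lies within the person, so its variance is (1 − ρ) times the independence value. The rate is about P(|Z| > 1.96/√(1 − ρ)).
- ρ = 0.3: 1.96/√0.7 = 2.34, giving 1.9%
- ρ = 0.5: 1.96/√0.5 = 2.77, giving 0.6%
- ρ = 0.7: 1.96/√0.3 = 3.58, giving under 0.1%

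Simulation gave 1.9%, 0.6% and under 0.1%, against about 5% for the within-participant test.

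**4. Power of group-by-time for 8 points on the RPQ-13 at week 6, closing by week 12.** The group differences are (0, 8, 0). Their squared deviations from their mean sum to 64 × 2/3 = 42.67. The interaction noncentrality is (25/2) × 42.67/[9.9² × (1 − ρ)] = 533.3/[98.01 × (1 − ρ)], which is 10.9 at ρ = 0.5. Simulated power, without a participant term against with the within-person error term:

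| ρ | No participant term | Within-person error |
|---|---|---|
| 0.3 | 51% | 69% |
| 0.5 | 48% | 83% |
| 0.7 | 45% | 97% |

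**The case against.** The strongest reply is that two groups by three times is common shorthand for a split-plot ANOVA with time within person, and that an article may leave the error term to the full protocol or SAP. This stands in part. A reader might infer that the article makes time an ordinary factor and counts the three scores as independent. It writes no such equation, residual or degrees of freedom, so that stronger reading is not supported. The list of six variables does not support it either: it has no participant identifier, but it also omits time and the covariates, so it is not a full data specification.

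The reply does not dispose of the point, because the text is not merely silent. The abstract attaches an independent-samples test to the main model, while the Statistical analysis section reserves it for the secondary outcomes. An unpaired t-test at one visit, or on change scores, would be valid with one row per person, but that is not a group-by-time model over three visits. A separate SAP cannot remove the inconsistency from the published article.

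Three further reservations stand:
- A reader might infer simply that false positives are inflated. That applies to the sequence main effect, which averages baseline and both periods and is not the programme difference. For group-by-time or treatment received, the error runs the other way.
- The planned baseline covariates could absorb some between-person variation and shrink the distortions; the calculations include none.
- A participant term alone would not complete the crossover model.

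**Conclusion.** The point holds in conditional form. The article names group-by-time ANOVA/ANCOVA for a thrice-scored crossover outcome, labels it unpaired in the abstract, and states no within-participant structure. If an analyst fits what is named without a participant term, no reading of group gives a test at its nominal 5%: about 12% to 21% for the sequence main effect, about 1.6% to under 0.1% for group-by-time, and about 2% to under 0.1% for treatment received. The loss of power for group-by-time at the plan's own RPQ-13 difference is about 35 percentage points (83% to 48%) at ρ = 0.5. These sizes rest on assumed correlations of 0.3 to 0.7, equal groups of 25, complete data and no covariates; the power figures also rest on an SD of 9.9. If a repeated-measures ANOVA was intended, these error rates do not arise and the defect is one of wording, but the wording must then say so. The change should be made before analysis.

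**What to change.** In the Statistical analysis section, replace the ANOVA and 2-way ANCOVA for the RPQ with a linear mixed (repeated-measures) model that has the participant as the unit, through a random participant effect or a stated within-participant covariance. Include treatment, period and sequence, with baseline RPQ as a covariate. Alternatively, if week 6 alone is to be primary, use an ANCOVA with one row per participant, adjusted for baseline RPQ. In the abstract, delete the unpaired t-test from the description of this model.

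The cost is a change of wording and a few lines of SAS code. No new data, visits or participants are needed.
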